**Fig. 1 Fig1:**
[figure not shown]
Flow diagram of the pharmaceutical review intervention and improvements to the medication plan

Although the intervention being assessed will be carried out both on a professional level with the family physicians as well as with the patients and caregivers, the intervention results will be measured in every patient. The intervention on physicians/patients will not be blinded but the results will be measured blind.

### Usual practice (control group)

In the control group, the patients' treatment plans will be managed according to usual criteria and procedures, including an automatic warning system generated by the Self-Audit tool which is part of the electronic clinical record to identify safety problems: redundant treatments, polymedicated patients, side effects, and review of the treatment duration, among others [22].

### Measurements

The outcome variables will be obtained at baseline and after six months with a review of the pharmacological prescription module in the electronic clinical record made using a questionnaire which compiles electronic data. The review will not be blind with regards to the patient's allocation to either of the two study groups. However, the results will be subsequently evaluated blind. A data monitoring committee (DMC) is not needed in this monocentric academic trial with known minimal risks. All study-related information will be codified and stored securely at the study site.

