## Abstract

**Background:**

ATDOM is the Catalan home healthcare program at primary care level. Patients in the home care program are usually frail, elderly people with multiple comorbidities. They are often polymedicated, leading to a high risk of drug-related problems (DRPs). Our hypothesis is that the pharmacist-led individualized review of the pharmacotherapeutic plans of ATDOM patients will be effective in improving the quality of treatments by reducing DRPs in terms of indication, adequacy, effectiveness, and safety.

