## Background

A drug-related problem (DRP) occurs when, in the application and use of drugs, patients experience or are likely to experience problems associated with these drugs [1]. Studies carried out both in and outside Spain show very disparate data on the prevalence of DRPs, with between 3.9% [2] and 59% [3] of patients being affected. This difference in the percentage of DRPs between the different studies could stem from the differing concepts of DRP, in addition to patient typology. The incidence of DRPs is recorded for in-patients [4] and out-patients [5]. This latter group includes those receiving home care. There are a variety of factors which could increase the risk of DRPs in the home care setting: associated illnesses and polymedication (owing to greater life expectancy), sporadic contact with the physician in relation to chronic illnesses which do not require regular check-ups, healthcare via different providers, lack of teamwork by the interdisciplinary team, and scant patient’s information about their treatment [6]. A recent systematic review revealed a high prevalence of DRPs, particularly amongst home-dwelling elderly patients [7]. Certain categories of DRPs, such as adverse reactions to medication or medical interactions, are of considerable clinical significance as they can result in hospitalization [8]. In relation to the importance of DRPs in outpatients, while it is true that the majority of DRPs would not have caused the patient any harm, they could have affected the effectiveness of the treatment [9].

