### Study setting and patient sample

The study will be carried out at 10 primary care centers within the Camp de Tarragona Regional Health Authority (Catalan Health Institute) in the Tarragona province (Catalonia). Participation in the study by family physicians from these centers will be voluntary.

The patients from the participating physicians will be eligible if they receive care through the ATDOM program, if they are 65 years old or over, and if they have an active pharmacological treatment plan involving at least one drug. It will be up to the responsible physician to decide if there are any reasons why a patient may be excluded, for example, if their participation might cause them harm. Those patients who are taken into care homes or long-term nursing facilities, or who pass away during the period of the study will also be excluded from the analysis.

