	Therapeutic goal is reached but the intensity of the pharmacological treatment must be reduced	
	Not the most effective-efficient alternative	
**Safety**	History of allergy or other adverse reaction to the same medication or similar	Metformin is a drug which is not recommended for patients with glomerular filtration of < 30 ml/min/1.73 m^2^)
	Drug with contraindications	
	Therapeutic duplication	
	Drug-drug interaction	
	Drug-food interaction	
	Lack of analytical control	

After the review process, a meeting will be held between the pharmacist and the physician in charge in which the DRPs detected will be discussed (Fig. 1) and a series of recommendations for improvement and proposals for change will be made. The proposals might be: (a) suspending treatment of a drug, (b) changing the medication, (c) changing the dosage, (d) changing of posology, (e) starting a new treatment, (f) monitoring the clinical and/or analytical variables, and (g) interventions to encourage adherence to the treatment. Thereafter, the physician will make a global assessment of the improvement and adaptation treatment plan and in exercising his/her responsibility will decide to what degree and/or which points to adhere to in the plan. In any case, the proposals, their justification, the expected advantages and possible drawbacks will be explained and agreed with the patient and, if necessary, with the caregiver or responsible family member. The whole procedure will be recorded in the patient's clinical record.

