### Statistical methods

#### Sample size

Based on a review of the literature [7, 14], as well as an exploratory analysis of 100 patients eligible for the study, we assume that in our target patient population the proportion of patients with at least one DRP will be around 60% and we hope to be able to detect a reduction of ≥ 15% in the intervention group after six months. If we accept an alpha risk of 0.05 and a power of 80% in a bilateral contrast, and assume a 20% loss of patients in the process (patients who go into a care home, or into a long-term nursing facility, or who pass away during the study period), we need to include 216 individuals in each group (Fig. 2).

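### No clinical harm event is listed as an outcome, and deaths and facility admissions are left out of the analysis, so a favourable result would come with no safety comparison

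*Protocol article*

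**What the plan says.** The Abstract describes the population: "Patients in the home care program are usually frail, elderly people with multiple comorbidities". Under Intervention, the proposals that follow the pharmacist's review include "a) suspending treatment of a drug, (b) changing the medication, (c) changing the dosage", and also starting new treatment. The responsible physician "will decide to what degree and/or which points to adhere to in the plan", and proposals are explained to and agreed with the patient or caregiver, drawbacks included.

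The principal variables are DRPs (total, per patient, and patients with at least one) and polymedication (drugs per patient, and patients on 8 or more). Table 1 gives the key secondary outcomes as proposals issued and proposals implemented. The Variables section adds sociodemographic and clinical descriptors, the treatment plan by ATC code, DRP type and adherence.

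Study setting and patient sample removes from the analysis patients who die or move to a care home or long-term nursing facility during the study. Data analysis states that the principal analyses follow intention to treat. Sample size says the planners "assume a 20% loss of patients in the process", and defines that loss as exactly these events.

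Measurements says: "A data monitoring committee (DMC) is not needed in this monocentric academic trial with known minimal risks". Study setting says: "The study will be carried out at 10 primary care centers within the Camp de Tarragona Regional Health Authority".

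Design offers the intervention to control patients if it proves effective. The Discussion, in the Abstract and in the main text, foresees extension to all ATDOM patients or to outpatients generally.

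**The concern.** The intervention acts by changing drug treatment, and such changes can harm as well as help. The listed outcomes describe prescriptions and process. Death, hospital admission, emergency visit and adverse event are not among them. The only clinical events the article says it will identify after randomisation, death and entry to a facility, are grounds for removal from the analysis.

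If the intervention arm had more of these events, no listed outcome would show it, and the patients concerned would be absent from the analysed set. A conclusion of effectiveness, and the extension that may follow from it, would rest on DRP and drug counts alone.

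The sentence that declines a DMC adds to the unease. It calls a 10-centre trial monocentric, and it asserts minimal risk without a citation or argument.

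**Working it through.** **1. The plan's own figure.** Inputs from Sample size: 60% with at least one DRP, a reduction of 15 (taken as absolute, to 45%), two-sided alpha 0.05, power 80%, loss 20%.

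- Pooled proportion: (0.60 + 0.45)/2 = 0.525.
- n = [1.96·√(2·0.525·0.475) + 0.8416·√(0.60·0.40 + 0.45·0.55)]² / 0.15² = 172.8, so 173 per arm.
- Allowing for loss: 173/0.80 = 216.25, which agrees with the stated 216 per group and 432 in total. A relative reading (60% to 51%) would need 598 per group, so the absolute reading is the one used.

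**2. Events removed from the analysis.** The 20% is defined as death or entry to a care home or nursing facility.

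- 0.20 × 432 = 86.4 patients in total.
- 0.20 × 216 = 43.2 patients per arm.

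**3. Precision of a comparison by arm.** With 216 per arm and 20% in each:

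- SE of the difference = √(2 × 0.20 × 0.80 / 216) = 0.0385.
- 95% half-width = 1.96 × 0.0385 = 0.075, or 7.5 percentage points.

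**4. Other event rates.** The article gives no rates for admissions or emergency visits, so these control rates are assumptions. Half-widths take the same rate in both arms. The last column is the increase detectable with 80% power at two-sided 0.05, 216 per arm.

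| Assumed control rate | 95% half-width (points) | Detectable increase (points) |
|---|---|---|
| 5% | 4.1 | 7.7 |
| 10% | 5.7 | 9.6 |
| 15% | 6.7 | 10.9 |
| 20% | 7.5 | 11.8 |
| 30% | 8.6 | 13.0 |

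At 20%, the detectable excess corresponds to about 43 against 69 patients with an event (216 × 0.318 = 68.7). None of these figures allows for patients sharing a physician, which Data analysis says will be considered.

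**5. How far the listed outcomes can register harm.** Table 2 counts as DRPs a missing necessary medicine, an unreached therapeutic goal, too low a dose, contraindications and interactions. A harmful withdrawal or switch could therefore appear as a DRP at six months, but only in a patient still in the analysis, and only as a prescribing-level marker. The drug-count outcomes improve when a drug is stopped, whatever follows. Neither kind of outcome records a clinical event.

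**The case against.** The strongest reply is that this is a condensed article about DRP reduction. The physician controls every change and the patient agrees to it. Adverse-event procedures may well be in the full protocol, which is not shown, and the study flow diagram is missing from the text at hand. Events by arm would be imprecise, and Measurements names only the prescription module as the data source.

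Much of this stands, and it rules out several stronger readings that a reader might infer:

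- *That the text contradicts the claim of minimal risk.* It does not. The Background remark that certain DRPs "are of considerable clinical significance as they can result in hospitalization" concerns the problems the review aims to reduce, and the 20% is a planning figure applied to both groups. Letting physicians exclude patients who might be harmed acknowledges some risk, not more than minimal risk. The claim is unsupported, not contradicted.
- *That all monitoring is waived, or that harm would reach no reviewer.* The article declines a DMC only, which is not in itself an error here. Other safety reporting cannot be judged from a condensed article.
- *That the trial measures no harm at all.* Some DRP types can register a harmful change, as shown above.
- *That the monocentric wording undermines the design.* All the centres belong to one health authority, and neither the sample size nor the analysis depends on the word.

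What the reply does not answer is what the article itself fixes: its outcome lists contain no clinical event, and it removes deaths and facility admissions from the analysis. The full document may say more about adverse-event handling, but both of these are stated choices.

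**Conclusion.** The point holds in limited form. No clinical harm event is a listed outcome, and about 86 of 432 patients (43 per arm) are expected to have an event that takes them out of the analysis, with no comparison by arm described. Their removal also conflicts with the stated intention-to-treat principle. As the article stands, a favourable result would say nothing direct about clinical safety, although extension is contemplated.

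The size rests on the article's 20%, assumed equal in the two arms. The ±7.5 points takes all 216 per arm as followed for these events and ignores clustering. A comparison of this kind is descriptive: it could show or bound a large excess, not exclude a modest one. The conflict between monocentric and 10 centres is a correction of wording.

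**What to change.** 1. For all randomised patients, report death and admission to a care home or nursing facility by arm over six months, with risk differences and 95% CIs that allow for physician clustering. The trial must already identify these events to apply its exclusion.
2. Add unplanned hospital admissions and emergency visits where the electronic clinical record holds them. That it does is an assumption to be checked.
3. Present these results beside any claim of effectiveness, and state that they are descriptive.
4. Reconcile the exclusion of these patients with the intention-to-treat statement.
5. Reconcile monocentric in Measurements with the 10 centres in Study setting, and either support the statement of minimal risk or drop it. No DMC is required.

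The cost is a protocol amendment, a few extra extraction fields, and intervals that will be wide and must be reported as such. The sample size and the principal outcomes stay as they are.

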### Variables

#### Principal variables

Drug related problems [23, 24]: Total DRPs, DRPs per patient, and number of patients with one or more DRP.Polymedication: number of associated drugs per patient and number of polymedicated patients. We define polymedication as the simultaneous consumption of ≥ 8 different drugs [25].

#### Secondary variables and co-variables

Sociodemographic data: age, sex, primary care team, socioeconomic status according to place of residence [26], household characteristics, caregiver, social/family support.

Clinical variables: Physical comorbidity: chronic pathologies such as diabetes mellitus, coronary heart disease and other types of heart disease, cerebrovascular disease, respiratory diseases, musculoskeletal diseases, diseases of the connective tissue and neoplasms.Psychological comorbidity: dementia, depression, anxiety and psychotic disorder.Charlson index. This refers to a global index of comorbidity which computes 19 items related to various pathologies which together with the patient's age is used to predict comorbidity after one year and after ten years [27].AMG (Adjusted Morbidity Groups) is an instrument for stratifying the population in relation to multimorbidity and complexity. It provides good explanatory results for indicators of healthcare resource usage, in particular for drug consumption [28].Barthel test. This measures the degree of the patient's dependence in basic day-to-day activities and its results are shown on an ordinal scale from 0 (maximum dependence) to 100 (total autonomy) [29, 30].Pfeiffer test. This questionnaire detects the existence and extent of cognitive decline by assessing the subject's responses to ten brief questions. It examines short- and long-term memory, orientation, information about daily life and calculation ability [31, 32].Complex chronic patient (CCP). This is defined as a patient with multimorbidity, extreme fragility or a unique condition which makes clinical management difficult. These are patients who use emergency hospital services very frequently, spending various periods in hospital throughout the year, they experience reductions in their personal autonomy either temporarily or permanently and are polymedicated [33].Advanced chronic patient (ACP). These are defined as patients with a limited life prognosis and high level of need, requiring palliative care and advanced decision planning [34].

Variables related to pharmacological treatment:Description of the pharmacotherapy plan using an ATC code (Anatomical, Therapeutic, Chemical classification system). This is a drug index organized by therapeutic group, which includes the system or organ which it acts upon, the pharmacological effect, the therapeutic indications and the chemical structure of the drug [35].Description of DRPs detected according to typology: indication, adequacy, effectiveness, safety (Table 2) [8].Adherence to the treatment by analyzing the medicines dispensed from the pharmacy office in relation to the dosage and prescribed dose. This will be examined after a period of six months. The adherence will be considered adequate if > 80% of the necessary doses have been taken.

Variables related to the procedure and result of the pharmaceutical intervention:Number of changes or improvement proposals sent by the pharmacist.Number of proposals implemented by the physician.

### Statistical methods

#### Sample size

Based on a review of the literature [7, 14], as well as an exploratory analysis of 100 patients eligible for the study, we assume that in our target patient population the proportion of patients with at least one DRP will be around 60% and we hope to be able to detect a reduction of ≥ 15% in the intervention group after six months. If we accept an alpha risk of 0.05 and a power of 80% in a bilateral contrast, and assume a 20% loss of patients in the process (patients who go into a care home, or into a long-term nursing facility, or who pass away during the study period), we need to include 216 individuals in each group (Fig. 2).

**Fig. 2 Fig2:**
[figure not shown]
Flow diagram of study: center allocation, sampling and monitoring

### Data analysis

The principal analyses will be carried out by intention to treat, taking the patients in each group according to their initial random assignment, independently from the adherence to the pharmaceutical intervention and the recommendations made. The results will be measured in individual patients, although the intervention will be largely directed to the attending physician in the form of instructions or change recommendations. In the analyses we will bear in mind the potential loss of independence that might occur in observations when patients are treated by the same physician (cluster effect). We will first compare both study groups to check that their baseline characteristics are similar. The principal result variables (dependent) will be the number of DRPs per patient, the proportion of patients with DRPs, the number of drugs per patient and the proportion of polymedicated patients. To assess the effects of the intervention on the dichotomous variables we will use multilevel logistic regression models with mixed effects using an Odds Ratio estimate (IC95%) of the intervention group with respect to the control group as an effect measure. To measure the effect on the continuous variables we will use linear regression models with random effect, estimating the differences in adjusted means (IC95%) for the intervention group versus the control group. The statistical significance will be established as *p* < 0.05. For these calculations, we will use the R statistical package.

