### Aim

The aim is to compare the effectiveness of a standardized pharmaceutical intervention for the review and optimization of pharmacological treatments in elderly patients on the ATDOM program with usual management practice.

In particular we want to determine the effectiveness of the program by way of a six-month intervention trial in order to (1) reduce DRPs per patient, and (2) reduce polymedication. In the intervention group, we will evaluate the implementation of proposals for change or improvements made by the physician in charge.

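### Four principal outcomes share a flat 0.05 threshold with no single primary outcome, ranking or success rule, although the sample size was calculated for only one of them

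*Protocol article*

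**What the plan says.** All references are to the protocol article.

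- **Data analysis.** Four dependent variables are called principal: "The principal result variables (dependent) will be the number of DRPs per patient, the proportion of patients with DRPs", then "the number of drugs per patient and the proportion of polymedicated patients". Mixed-effects logistic models cover the two proportions and random-effect linear models the two counts. One threshold follows for everything ("The statistical significance will be established as" p < 0.05).
- **Principal variables.** The DRP part is "Total DRPs, DRPs per patient, and number of patients with one or more DRP" and the polymedication part is "number of associated drugs per patient and number of polymedicated patients". That makes five variables. Table 1 (registration data set) gives the same five as primary outcomes.
- **Sample size.** One outcome is used: "the proportion of patients with at least one DRP will be around 60"%, with a hoped-for reduction of at least 15%. The error rates are fixed by "If we accept an alpha risk of 0.05 and a power of 80% in a bilateral contrast". With 20% loss this gives 216 per group.
- **Aim.** The order differs here: "1) reduce DRPs per patient, and (2) reduce polymedication". The first aim is therefore the count per patient, not the proportion used for the sample size.

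No section says which of these outcomes decides the trial, whether all must succeed, or how the 0.05 is shared among them.

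**The concern.** The Design section promises the intervention to control patients if it proves effective, and the Discussion foresees extending it to all patients in the program or to outpatients in general. The document does not define which result would establish effectiveness. As written, any one of four tests could be put forward, each at 0.05, and the 5% error rate used for the sample size would not describe the risk of a false claim.

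The outcomes can also disagree. Table 2 counts a missing necessary medicine as a DRP, and starting a new treatment is among the listed proposals. Resolving that problem removes a DRP and adds a drug. Fewer DRPs with an unchanged or higher drug count is a foreseeable result, and no rule says how it would be read.

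**Working it through.** **1. Reproduce the planned size.** Inputs from Sample size: control proportion 0.60; reduction 0.15, read as absolute, so 0.45; two-sided alpha 0.05; power 80%; loss 20%.

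n = [z(0.975)·√(2·p̄·(1−p̄)) + z(0.80)·√(p1(1−p1) + p2(1−p2))]² / (p1−p2)², with p̄ = 0.525

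= [1.960 × 0.7062 + 0.8416 × 0.6982]² / 0.15² = 172.8, so 173 evaluable per group.

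Dividing by 0.80 gives 216.0 from the unrounded value and 217 from 173 rounded up, against 216 stated. A relative reduction of 15% (60% to 51%) would need 478 evaluable per group, so only the absolute reading fits. The planned size thus belongs to one outcome, the proportion with at least one DRP, at an unsplit 0.05.

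**2. Family-wise error for four tests at 0.05.**

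Independent: 1 − 0.95⁴ = 1 − 0.8145 = 18.5%, and 18.5/5 = 3.7 times nominal.

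The outcomes form two related pairs (DRP count and any DRP; drug count and polymedicated), so independence gives too high a figure. The protocol states no correlations. The values below are assumptions, evaluated by simulating correlated normal test statistics:

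| Correlation within a pair | Between pairs | At least one false positive |
|---|---|---|
| 0.3 | 0.3 | 17% |
| 0.5 | 0 | 17% |
| 0.7 | 0.3 | 15% |
| 0.8 | 0.3 | 15% |
| 0.9 | 0.5 | 13% |
| 0.8 | 0.8 | 11.4% |

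The lowest value is 11.4/5 = 2.3 times nominal. A patient-level null simulation gave 14.7% to 16.6%, inside this range. It assumed 173 per group, 60% with at least one DRP, drug count with mean 9 and SD 4, and a threshold of 8.

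**3. Cost of two repairs.** Power at 173 evaluable per group is Φ[(0.15·√173 − z·0.7062)/0.6982].

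- One primary outcome at 0.05 (z = 1.960): Φ(0.843) = 80.0%.
- Equal Bonferroni split over four, 0.05/4 = 0.0125 (z = 2.498): Φ(0.299) = 61.8%. Restoring 80% would need 246 evaluable, or 246/0.80 = 308 recruited, per group.

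Naming one primary outcome keeps both the power and the 216.

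**4. Compare the lists.** Table 1 and Principal variables name five outcomes, and Data analysis names four. The missing one is total DRPs. It is an arm total, so it depends on how many patients are analyzed in each group. At fixed group sizes it carries the same information as DRPs per patient.

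**The case against.** Five points can be made on the other side.

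- **The text leans towards DRPs.** The hypothesis speaks of reducing DRPs and does not mention polymedication, the first aim is about DRPs, and the trial is sized on a DRP outcome. If only the two DRP measures competed, the family-wise error would be 1 − 0.95² = 9.75% if independent and about 8% at an assumed correlation of 0.7 to 0.8. This has some force, but polymedication is the second aim and both drug outcomes are called principal. Even inside the DRP domain, the aim and the sample size point to different measures.
- **An analysis plan may handle multiplicity.** Adjustment or ordering of secondary tests can be left to that document. Which outcome is primary is protocol and registry content, and this article already fixes several principal outcomes and one threshold.
- **Five tests.** A reader might infer five tests from Table 1. The document does not support that, because total DRPs has no model in Data analysis.
- **Late registration.** Enrolment began in March 2020 and registration was in March 2023. A reader might infer that the outcomes were chosen late. The dates do not show that; they mean only that the registry entry is no evidence of a ranking fixed before enrolment.
- **DRPs per patient as primary.** A reader might infer that the same sample supports it. Under negative binomial counts matched to 60% and 45% with any DRP, power is high, 96% or more. But the mean is then m = k(P0^(−1/k) − 1), with P0 of 0.40 and 0.55. For k = 2 it falls from 1.16 to 0.70 (40%), and for k = 0.5 from 2.63 to 1.15 (56%). The document states no mean, variance or expected fall for the count, so this is not established.

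**Conclusion.** The concern stands for the four outcomes that the analysis covers. The plan does not say which result decides the trial, and its sample size supports one of them at an unsplit 0.05. The family-wise error is 18.5% under independence and about 11% to 17% under assumed positive correlations, or roughly 2.3 to 3.7 times 5%.

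Two assumptions carry that range: that significance on any one outcome would be claimed as effectiveness, and the correlations themselves. Neither is in the document. The inflation is therefore what the wording permits, not a rule that the plan states, and no single multiple should be given as fact. Total DRPs adds an inconsistency between sections and nothing to the error rate.

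**What to change.** - In Table 1 and the registry entry, Principal variables and Data analysis, name one primary outcome: the proportion of patients with at least one DRP at six months, tested at two-sided 0.05. This is the outcome for which 216 per group was calculated.
- Make DRPs per patient, number of drugs and proportion polymedicated secondary. Either test them in a prespecified order, stopping at the first non-significant result, or report them without confirmatory claims. The order just given is one valid choice among several.
- Reconcile the outcome lists and report total DRPs descriptively.
- If the sponsor prefers DRPs per patient as primary, first show its power from a stated mean, variance and expected reduction.
- Date the change and make it before any between-group comparison of outcomes. Unblinding is not a clean milestone here, because the Measurements section says that the outcome review is not blind to allocation. Table 1 gives the status as recruiting.

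The cost is wording in the protocol, analysis plan and registry. Sample size, design and conduct do not change. The small downside is that the other three outcomes cannot by themselves be claimed as proof of effectiveness.
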